### Sample size and power calculation

To assess implementation based on usage and uptake, we will treat the sample size calculated for effectiveness as a convenience sample. Because usage and uptake are being analyzed descriptively with no baseline data and no over-time comparison, it is not appropriate to calculate power for these outcomes.

To assess effectiveness based on per-end-user stage of change outcomes, our target sample size calculation is based on 12 available sites. Based on our previous RCT of 528 African American/Black women recruited nationally, [19] we expect to see an approximately 7.3% difference in the rate of risks behaviors achieving action or maintenance from 0 to 5.5 months, with a common error variance of approximately 28.7%. With paired two-sided tests, at a power of 0.80 and a significance level of 0.05, we would require at least 125 subjects to detect an effect of at least this magnitude. Because end-users are nested within sites, we also must account for within-site clustering. Based on published intra-class correlation coefficient (ICC) data from 61 clinical practices in 8 practice based research networks on risks such as smoking, diet, and exercise, we anticipate an ICC of 0.012 and a design effect of 1.3 [33]. Based on this design effect, we require at least 160 end-users, or 13 end-users per site. If we anticipate only about 2/3 of end-users to provide outcome data (consistent with our previous study), then we must enroll approximately 240 users, or 20 end-users per site, to detect a change in our outcome from 0 to 5.5 months.

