#### Quantitative data collection and measures

We will quantitatively evaluate implementation outcomes using two proxy measures for implementation: uptake and usage. Uptake will be measured at the end-user level as a binary indicator of whether the end-user logged in to the Gabby System at least once. Usage will be measured also at the end-user level as the number of logins to the Gabby System and the number of minutes spent using Gabby. Usage and uptake will be collected at 3 and 5.5 months.

In addition, following the organizational readiness interview, community partners will be asked to complete a corresponding scale based 33-question Qualtrics XM® survey that will be used to assess organizational readiness while examining affirming, contradictory or conflicting findings elicited during the organizational readiness interview. Participating community partner staff will receive the survey via email from the academic research staff and will be allotted 72 h from the time that they finish their organizational readiness interview to complete the quantitative survey. The purpose of the Likert scale based Qualtrics XM® survey is to complement the organizational readiness interview and serve as a validation of barriers and facilitators identified at the site. Responses along the 5-point Likert scale will consist of Strongly Disagree (1), Disagree (2), Neutral (3), Agree (4), Strongly Agree (5). This approach will allow for rapid data collection and timely turnaround of analysis and stratification of results by type of staff for actionable steps within a relatively short timeframe at every community site during this critical pre-launch phase.

We will evaluate the clinical effectiveness of the intervention through reports produced by the Gabby System server. For each client/patient we will track: (1) baseline stage of change data obtained for each risk identified during the client/patient’s interaction with the Gabby System; (2) follow-up stage of change data to identify the progression (or regression) in the changes associated with each health risk; (3) risk resolution based on the percentage of subjects reaching the action and maintenance stage for each risk at 3 months and 5 ½ months during the implementation period.

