To assess the effectiveness of Gabby, we will measure the rate of risk behaviors per subject at action and maintenance. Stage of change data will be collected at the initial assessment, at 3 months, and again at 5.5 months, and then compared across the three data collection points for triggered risks. We anticipate that subjects receiving an effective Gabby intervention should see a greater number of risk behaviors, from baseline to 3 and then 5.5 months, that have reached the action or maintenance stage of change. We will also assess the rate of risk behaviors per subject progressing forward on the stage of change scale. We will test for the effectiveness of Gabby by using a Poisson model to regress our stage of change rate outcomes on data collection time point, with site fixed effects. In addition, for each risk, a logistic regression model will be used to regress a binary measure of whether that risk had either remained at the action or maintenance stage or progressed forward, data collection time point, with site fixed effects.

Finally, we will run analyses to determine whether Gabby was differentially effective conditional on baseline stage of change. This will be done by restricting the data only to risks that were reported at “pre-contemplation” at baseline; then by calculating the rate that remained at “action” or “maintenance” or progressed forward, and finally by regressing that rate on the period of data collection using a Poisson model with site fixed effects. This procedure will be repeated by restricting the data to risks reported at “contemplation” at baseline, and again by restricting risks reported at “preparation” and then “action” stages of change. All statistical tests will be run at alpha level a = 0.05 and performed using the R programming language, version 3.4.3 [45].

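### The study is sized on paired within-woman tests, but the stated effectiveness model has no term linking a woman's repeated records, so its standard errors are not valid as written

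*Protocol article*

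**What the plan says.** Under Sample size and power calculation, the protocol article plans on an "approximately 7.3% difference in the rate of risks behaviors achieving action or maintenance from 0 to 5.5 months". The variability behind that figure is given as a "common error variance of approximately 28.7" per cent. It concludes: "With paired two-sided tests, at a power of 0.80 and a significance level of 0.05, we would require at least 125 subjects". It then multiplies by a design effect of 1.3 for clustering within sites (160 women) and divides by a two-thirds outcome rate (240 enrolled).

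Under Quantitative analysis, the outcome is a per-woman rate of risk behaviours at action or maintenance, recorded at the initial assessment, 3 months and 5.5 months. The test of effectiveness is described as "using a Poisson model to regress our stage of change rate outcomes on data collection time point, with site fixed effects". Two further sets of models are built in the same way: a logistic regression for each risk, and Poisson regressions restricted to risks at a given baseline stage. In all of them the only stated terms are time point and site. The one multilevel model in the section is for staff readiness scores, not for end-users.

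**The concern.** The planned sample size works because each woman is her own control. The stated model does not use that. Site fixed effects remove differences between sites; they do not account for three records coming from the same woman. A Poisson likelihood also fixes the variance at the mean. Risks within one woman tend to move together, so the spread of her counts over time need not follow that rule.

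Effectiveness is one of two co-primary aims (Aims and objectives), and the design is a single cohort. The within-woman change over time is therefore the whole of the quantitative evidence on effectiveness. A standard error that is too small could support a false claim; one that is too large could hide a real change.

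**Working it through.** **1. Reproduce the plan's figure.** Inputs from Sample size and power calculation: difference δ = 0.073, variability 0.287, two-sided α = 0.05, power 0.80, paired.

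n = [SD × (1.960 + 0.842) / δ]² = [0.287 × 2.802 / 0.073]² ≈ 121.3, so 122 by the normal approximation. The noncentral t gives 124, with power 0.806 at 125. The stated 125 is reproduced.

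This needs 28.7% to be the SD of the paired change. Read literally as a variance (SD = √0.287 = 0.536), it gives 423. The later steps also follow: 125 × 1.3 = 162.5 (stated 160), and 160 ÷ (2/3) = 240.

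**2. What the pairing contributes.** Let ρ be the correlation between a woman's rates at two occasions and σ the SD at one occasion. The SD of the change is σ√[2(1 − ρ)]. An analysis treating occasions as independent uses SE = σ√(2/n), which is larger than the paired SE by 1/√(1 − ρ). Holding the SD of the change at 0.287, power at n = 125 is Φ[0.073 × √(125(1 − ρ)) / 0.287 − 1.960]:

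| ρ (assumed) | SE inflation | Women needed | Power at 125 |
|---|---|---|---|
| 0 | 1.00 | 122 | 81% |
| 0.25 | 1.15 | 162 | 69% |
| 0.5 | 1.41 | 243 | 52% |
| 0.75 | 2.00 | 485 | 30% |

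This assumes that the variance at each occasion is itself estimated correctly, which Poisson does not guarantee.

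**3. The stated Poisson model.** It was simulated with 160 women, 12 sites, three complete occasions, counts of risks at action or maintenance with log(number of risks) as offset, and time and site terms. There were 300 runs per scenario, with no true change. Not in the document, so assumed: mean risks per woman, baseline rate, SD of the underlying rate between women, and correlation of the underlying rates (latent, so higher than the correlation of observed rates).

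| Risks | Baseline | Latent corr. | Between-woman SD | SD of change | Model SE ÷ true SE | Type I error as stated | Type I error clustered on woman |
|---|---|---|---|---|---|---|---|
| 5 | 0.30 | 0.8 | 0.25 | 0.323 | 1.21 | 1.3% | 4.0% |
| 5 | 0.30 | 0.5 | 0.20 | 0.362 | 1.06 | 2.7% | 2.3% |
| 10 | 0.30 | 0.5 | 0.20 | 0.281 | 0.89 | 11.0% | 4.3% |
| 25 | 0.30 | 0.8 | 0.25 | 0.199 | 0.73 | 15.0% | 4.3% |
| 25 | 0.30 | 0.5 | 0.20 | 0.235 | 0.70 | 16.0% | 4.3% |
| 25 | 0.30 | 0.3 | 0.25 | 0.319 | 0.45 | 37.3% | 7.3% |
| 25 | 0.15 | 0.3 | 0.20 | 0.259 | 0.39 | 47.3% | 6.7% |

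With 300 runs, the Monte Carlo standard error at a true 5% is √(0.05 × 0.95/300) = 1.3 points, so the clustered column is compatible with 5%. A second, separate simulation of the same model gave 1.3% to 34% as stated, about 8 to 9% where the SD of the change was near 0.287, and 2 to 5% with clustering.

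**4. Direction.** The ratio of model SE to true SE crosses 1 within the table. With few risks and high correlation the stated test is conservative; with many risks it is anti-conservative.

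**The case against.** The strongest reply is that this is a journal article. It gives the mean model and is silent on variance estimation, and sandwich variance clustered on the woman is compatible with its sentence. That stands in part: a fuller plan may already add it, and then the error rates above would not apply. But the article does give the family, the regressor and the device for sites, and it names a multilevel model where one is intended, for staff scores. Beside a sample size that rests on "With paired two-sided tests, at a power of 0.80 and a significance level of 0.05", this is a stated model that does not match its stated sizing, not just an omitted detail.

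A second reply is that the two errors partly cancel. True, and in some scenarios the result lands near 5%, but nothing in the text secures that.

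A third is that the Abstract plans 25 to 50 women per site, 300 to 600 in all, so 200 to 400 with outcome data at the two-thirds rate. With ICC 0.012, a correlation of 0.5 and occasions treated as independent, power would be about 64 to 86%. Larger numbers recover power but do not repair the type I error.

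Some stronger readings are not supported:
- **Power falls from 80% to about 51%.** This holds only at a within-woman correlation of 0.5, which the document does not give.
- **Power is close to zero.** This requires entering a fractional share as the Poisson response. A Poisson model for a rate ordinarily means counts with an offset, and the section itself speaks of a number of risk behaviours.
- **The outcome is shown elsewhere to be a bounded per-woman share.** The data collection item "risk resolution based on the percentage of subjects reaching the action and maintenance stage for each risk" is a proportion of women for each risk, a different quantity from the per-woman rate.
- **Poisson must be replaced.** Clustering on the woman was enough in the simulations.

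**Conclusion.** The point holds in this form: the effectiveness test as stated does not match the paired test that yields 125 women, and followed as written its standard error for the time effect is not valid. The per-risk logistic and baseline-stage Poisson models have the same gap; they were not sized here.

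The size is a range, not a figure. Type I error ran from about 1% to 47% over the assumed scenarios, and about 8 to 11% where the simulated SD of change was closest to the planning value. The loss from ignoring pairing alone runs from none at zero correlation to power of 30% at 0.75. A reader might infer that the test is plainly anti-conservative, or plainly underpowered. The document supports neither, because it gives neither the number of risks per woman nor the within-woman correlation. Since this is the test of a co-primary aim, the text should be settled before the analysis.

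**What to change.** In Quantitative analysis, add a sentence saying that every time-point model (the main Poisson models, the per-risk logistic models and the baseline-stage models) accounts for repeated records on the same end-user. Use GEE or sandwich variance clustered on the end-user. An end-user random intercept is an alternative for the rate models only if overdispersion is also allowed for, since the intercept alone does not absorb variation within a woman over time.

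State that the number of triggered risks enters the rate models as offset or denominator. Report the 0 to 5.5 month change in percentage points, so that it can be read against the 7.3-point planning effect.

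Poisson may be kept with clustered robust variance; a binomial or quasi-binomial model is acceptable but not required. The cost is a sentence of text and a few lines of R, with no new data or participants.

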### The Gabby System: an evidence-based preconception care intervention

Health information technology (HIT) is an important tool for information sharing, enhancing consumer engagement, and facilitating shared decision making to improve the quality and efficiency of care [20, 21]. HIT can be leveraged to develop culturally tailored, low cost, and convenient interventions to better reach and reduce disparities in health outcomes for socially disadvantaged, underserved and health disparity populations [22]. Technology-based interventions (e.g. mHealth, eHealth) can be leveraged to enhance patient engagement, support decision making, and improve patient-provider communication. The Gabby System, here forth Gabby, is a HIT intervention programmed to screen for PCC-related risk factors and identify health and social care needs across several domains including: genetic health history; immunizations and vaccinations; sexual and reproductive health; infectious disease; health conditions and medication use; alcohol, tobacco and other drug use; social and emotional well-being; relationships and relational health; healthcare access and affordability; social determinants of health; nutrition and physical activity; and environmental wellness [18]. Gabby is an Embodied Conversational Agent (ECA) that provides comprehensive health promotion and education for each domain, assesses one’s readiness for behavior change, and tailors behavior modification strategies to the user’s risk-specific stages of change [19]. Using conversational speaking style, ECA’s are designed to emulate expert communication skills by focusing on the most salient information, evaluating the patient’s level of understanding, and repeating or elaborating information as necessary [23–25]. ECA’s use speech, gaze, hand gestures, intonation, and other nonverbal modalities to capture the experience of human face-to-face conversation with the end user. Gabby is theoretically grounded in Prochaska and DiClemente’s Transtheoretical Model [26] and uses a variety of health education and motivational strategies to support users’ progression through pre-contemplation, contemplation, preparation, action and maintenance stages of change - thus demonstrating that health behavior change is a process rather than a singular event. Users create an individualized “My Health To-Do List” (MHTDL) that they can work on at their own pace and/or discuss with their healthcare provider. Specifically designed and informed by Black and African American women, [27] the efficacy of Gabby has been demonstrated in two randomized controlled trials, and has successfully identified and resolved health risks for these women [18, 19]. While Gabby has shown strong evidence to support health behavior change in the research setting, the capacity to which these outcomes translate into the daily lives of Black and African American women and in community-based clinical contexts has yet to be determined. Utilizing HIT as an implementation modality has the potential to increase scalability, improve fidelity of information and reduce staff training time.

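### The forward-progress and remained-or-progressed outcomes have no backward counterpart, so with no control arm the forward rate can suggest benefit when equal movement both ways leaves no net change

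*Protocol article*

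**What the plan says.** The protocol article, under Quantitative data collection and measures, says the Gabby server will supply "follow-up stage of change data to identify the progression (or regression) in the changes associated with each health risk". The section describing the Gabby System gives the scale in order: "pre-contemplation, contemplation, preparation, action and maintenance stages of change".

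The Quantitative analysis section then fixes the effectiveness outcomes:

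- The main one is a level: "we will measure the rate of risk behaviors per subject at action and maintenance". The sample size section is built on this outcome, planning for an "approximately 7.3% difference in the rate of risks behaviors achieving action or maintenance from 0 to 5.5 months" with paired two-sided tests.
- A second is directional: "We will also assess the rate of risk behaviors per subject progressing forward on the stage of change scale". It shares a Poisson model on data collection time point, with site fixed effects, with the first.
- A third, modelled by logistic regression for each risk, is "a binary measure of whether that risk had either remained at the action or maintenance stage or progressed forward".

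The third rule is repeated as a rate within strata of baseline stage: pre-contemplation, contemplation, and "again by restricting risks reported at “preparation” and then “action” stages of change". Maintenance is not among the strata. Stages are also to be "compared across the three data collection points for triggered risks", without saying how. No outcome or model for backward movement is named.

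**The concern.** The article says backward movement is tracked, then defines two of its three effectiveness outcomes so that they credit forward movement and lose part of the backward movement. The study is a single cohort and the stages are self-reported. Some risks will be reported at a different stage on a second occasion for reasons unrelated to the intervention, and no comparison group shows how many. The rate of backward moves, available from the same records, is the natural yardstick for the forward rate.

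Effectiveness is one of two co-primary aims, and the Discussion points to scale-up. A reader given the forward rate alone could take instability for benefit. That reader also could not tell in which risk domains women slipped back among the lower stages.

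**Working it through.** **Which outcome is powered.** The inputs from the sample size section are a difference of 0.073, variability of 0.287 (used here as the standard deviation of the paired difference), two-sided 0.05 and power 0.80. Then n = (0.287 × (1.960 + 0.842) / 0.073)² = 121.3, so 122; the exact paired t calculation gives 124. The article states 125, so the figure reproduces closely. It refers to the action-or-maintenance level, not to the forward rate, and nothing below changes it.

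**Backward moves against each outcome.** Five ordered stages give 5 × 4 / 2 = 10 backward moves. The article does not state the reference point for progress; baseline is assumed here.

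| Move, baseline to follow-up | Number | At action or maintenance | Forward | Remained or progressed |
|---|---|---|---|---|
| Action or maintenance to any lower three stage | 6 | falls from 1 to 0 | 0 | 0 |
| Maintenance to action | 1 | stays 1 | 0 | 1 if either stage counts as remaining; 0 if the same stage is required |
| Contemplation to pre-contemplation; preparation to contemplation or pre-contemplation | 3 | stays 0 | 0 | 0 |
| For comparison: no change at one of the lower three stages | – | stays 0 | 0 | 0 |

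The last two rows are identical, so the three lower-stage falls cannot be told apart from no change on any named outcome.

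**Balanced movement.** Let f be the share of risks moving forward and b the share moving back.

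- The forward outcome equals f whatever b is. Net movement is f − b.
- If f = b, net movement is 0 and the forward outcome is still f. Since f + b cannot exceed 1, f can then lie anywhere from 0 to 50%.
- As an assumed example, f = b = 27% gives net 0 and a reported forward rate of 27%.
- Measured from baseline, the forward rate is 0 at baseline by construction. A model on time point that includes baseline can then only show a rise.
- The level outcome behaves differently. Its change is the share crossing up into action or maintenance minus the share crossing down, so balanced crossings leave it at 0.

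**Baseline strata under the remained-or-progressed rule.**

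| Baseline stage | Follow-up stages scored as failure | What failure means |
|---|---|---|
| Pre-contemplation | pre-contemplation | no change only |
| Contemplation | pre-contemplation, contemplation | falls and no change mixed |
| Preparation | pre-contemplation, contemplation, preparation | falls and no change mixed |
| Action | pre-contemplation, contemplation, preparation | falls only |
| Maintenance (not listed) | would be pre-contemplation, contemplation, preparation (plus action, if remaining means the same stage) | would be falls only |

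The stratum that can only hold or improve is analysed; the one that can only hold or fall is not.

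**The case against.** The strongest reply is that the powered outcome is a two-sided net level. It falls when risks drop below action, and balanced movement across that threshold would not make the programme look effective on it. Six of the ten backward moves also score as failures on the per-risk binary. In the baseline-action stratum every failure is a fall, so one minus the success rate is the regression rate from action. All of this stands. A reader might infer that every outcome runs one way, or that regression cannot be seen at all; the definitions support neither.

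A reader might also infer that counting maintenance-to-action as success is an error. The article treats action and maintenance together as risk resolution in its measures, sample size and analysis sections, so a risk moving between them is still resolved on its own terms. What stands is only that the wording of the binary allows two readings.

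The last reply is that this is a condensed article and a transition table may be planned in a document not shown. That is a fair caution. But the article itself states the outcomes, models and strata, and the point rests on how those are defined. The planned comparison across time points does not say that backward moves will be reported.

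**Conclusion.** The concern holds as a definition and reporting gap in the additional effectiveness outcomes. Three of ten backward moves are pooled with no change, one has an ambiguous score in the binary, and the maintenance stratum is missing. The forward rate cannot separate benefit from balanced instability, so taken alone it can mislead. The main outcome, the powered test and the sample size are unaffected.

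Two further inferences are not supported. The article does not present regression as a harm measure, so it should not be called the study's only harm signal. And the assumed 27% should not be set against the planned 7.3%: the first is a hypothetical forward rate, the second a change in the action-or-maintenance level.

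The size in practice is unknown. The article gives no transition frequencies and does not say whether a risk at maintenance at baseline counts as triggered. The conclusion assumes that progress is measured from baseline.

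**What to change.** In the Quantitative analysis section:

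1. Beside the forward rate, report the per-woman rate of risks that moved back at least one stage from baseline to 3 months and to 5.5 months, with its confidence interval, overall and by risk domain. A full stage-transition table would serve as well.
2. Include risks at maintenance at baseline wherever these are recorded.
3. State that the forward rate will not be interpreted as effectiveness without the backward rate.
4. State whether remaining, in the per-risk binary, means staying within the combined action-or-maintenance category or in the same stage. Keep the combined category for risk resolution, and let the transition table show moves from maintenance to action.

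The cost is a few lines of wording and one more table from data already collected. The downside is a possibly less favourable reading of the forward rate.

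### The progression outcomes have no usable baseline value, so regressing them on time point, overall or by baseline stage, does not test whether Gabby works

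*Protocol article*

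**What the plan says.** All of this is in the protocol article, Methods, Quantitative analysis.

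- **Visits.** Baseline is one of the visits compared: "Stage of change data will be collected at the initial assessment, at 3 months, and again at 5.5 months, and then compared across the three".
- **Leading outcome.** "we will measure the rate of risk behaviors per subject at action and maintenance".
- **Forward movement.** "We will also assess the rate of risk behaviors per subject progressing forward on the stage of change scale".
- **Test of effectiveness.** Gabby is tested by "using a Poisson model to regress our stage of change rate outcomes on data collection time point, with site fixed effects". The plural outcomes take in forward movement, which is introduced in the sentence before.
- **Composite, risk by risk.** A logistic model for each risk has as its outcome "a binary measure of whether that risk had either remained at the action or maintenance stage or progressed forward", again with time point as regressor and site fixed effects.
- **By baseline stage.** To "determine whether Gabby was differentially effective conditional on baseline stage of change", the plan starts by "restricting the data only to risks that were reported at “pre-contemplation” at baseline", computes the composite rate, and ends by "regressing that rate on the period of data collection using a Poisson model with site fixed effects". It repeats this for contemplation, preparation and action.

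The study is a cohort with no control arm (Methods, opening paragraph), so time is the only contrast. For uptake and usage, the same section recognises that no baseline value exists and describes them at follow-up only. It makes no such restriction for the change outcomes.

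**The concern.** To have progressed, or to have remained, a risk needs an earlier visit to be compared with. At the initial assessment there is none. A model that regresses such an outcome on time point, with baseline among the time points, compares a value fixed by definition with an observed one.

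The stage-restricted fits show this most clearly. Once risks are selected on their baseline stage, the direction of change is largely settled before follow-up: early-stage risks can only rise from zero, and action-stage risks can only fall from 100%. Ordinary fluctuation would then appear as benefit in three strata and harm in the fourth, and the plan proposes to read that contrast as differential effectiveness. Effectiveness is one of two co-primary aims, and these fits supply its per-risk and by-stage evidence.

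**Working it through.** **1. The planned figure, and what it rests on.** Sample size and power calculation uses a 7.3% difference in the action/maintenance rate from 0 to 5.5 months and 28.7% for error (called a variance, used as a standard deviation). Paired normal approximation: ((1.96 + 0.8416) × 0.287 / 0.073)² = 121.3. The noncentral t gives 124, against 125 stated. The calculation therefore reproduces, and it concerns only the outcome that has a true baseline.

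**2. Baseline values by definition (reference visit = baseline).**
- Forward movement: 0% at baseline.
- Composite, strata at pre-contemplation, contemplation or preparation: nothing is at action and nothing has moved, so 0%.
- Composite, action stratum: 100% if being at action counts as having remained.
- Composite, all risks: the only sensible baseline coding is being at action/maintenance.

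**3. Why the overall composite drifts.** At follow-up every risk at action/maintenance counts, since it either remained there or moved forward to get there. Risks that moved forward but are still below action count as well. Hence:

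composite at follow-up = rate at action/maintenance + rate of forward moves that stop short of action.

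The second term has no counterpart at baseline. It is the drift when nothing truly changes.

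**4. Size under no change.** Assumptions, none from the protocol: true stage constant; true stage mix 25/25/20/15/15% from pre-contemplation to maintenance; each report is off by one stage with probability e, half up and half down; a misreport beyond either end stays at the end stage.

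Drift = 0.25·(1−e/2)(e/2) + 0.25·[2(e/2)(1−e) + (e/2)²] + 0.20·(e/2)(1−e).

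At e = 0.2: 0.25×0.09 + 0.25×0.17 + 0.20×0.08 = 0.0225 + 0.0425 + 0.0160 = 0.081.

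Baseline action/maintenance at e = 0.2: 0.20×0.1 + 0.15×0.9 + 0.15×1 = 0.305. It is also 0.305 at follow-up.

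| e | Composite at baseline | At follow-up | Drift (points) |
|---|---|---|---|
| 10% | 30.25% | 34.65% | 4.4 |
| 20% | 30.50% | 38.60% | 8.1 |
| 30% | 30.75% | 41.85% | 11.1 |

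**5. By baseline stage at e = 0.2.** Pre-contemplation: share reporting it at baseline 0.25×0.9 + 0.25×0.1 = 0.25; later reported higher 0.25×0.9×0.1 + 0.25×0.1×0.9 = 0.045; ratio 18%. Action: share 0.20×0.1 + 0.15×0.8 + 0.15×0.1 = 0.155; later at action or maintenance 0.02×0.1 + 0.12×0.9 + 0.015×1 = 0.125; ratio 80.6%. The same steps give 15.5% for contemplation and 14.8% for preparation.

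| Baseline stage | Baseline | Follow-up |
|---|---|---|
| Pre-contemplation | 0% | 18.0% |
| Contemplation | 0% | 15.5% |
| Preparation | 0% | 14.8% |
| Action | 100% | 80.6% |

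**6. A second null model.** Here the stage distribution is constant and uniform, and 10%, 20% or 40% of risks are re-drawn at random in each interval (160 women, 10 risks each, 12 sites, 200 datasets per setting). The planned Poisson model with site fixed effects, by likelihood-ratio test at 0.05, rejected as follows:
- action/maintenance: 0% in all three settings;
- forward movement: 100% in all three;
- pre-contemplation stratum: 100% in all three;
- action stratum: 0%, 93% and 100%, in the direction of harm.

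**7. The per-risk logistic test.** Using the assumptions of step 4, one risk per model, visits treated as independent, no site effects and a joint test of time (4,000 datasets per setting), false rejection at e = 10%, 20% and 30% was about 0%, 13% and 51% with 160 women. It was about 0%, 2% and 8% with 60 women. A variant with site fixed effects and a slightly larger drift gave 2–3%, 37–46% and 80% with 160 women.

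**The case against.** **The powered test is sound.** This stands in full. The action/maintenance rate is defined identically at all three visits and stayed flat in both null models. The other analyses are introduced as additions. A reader might infer that the whole effectiveness evaluation fails; the document does not support that.

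**Status could be judged from visit to visit.** The wording leaves room for this. A risk at pre-contemplation at baseline that reaches action by 3 months can remain there at 5.5 months, so the composite is not meaningless in that stratum. Measures and data collection also ties progression to follow-up data. If only follow-up visits are modelled on this reading, the structural zero disappears. The time term then compares movement in 3–5.5 months with movement in 0–3 months, which does not test change from baseline.

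**Baseline could simply be dropped, with change still measured from baseline.** The text does not say so. The coefficient would compare 5.5 with 3 months. Under pure reporting error there would be no drift between those visits, but under the random movement of step 6 forward movement still rejected in 100% of null datasets, because movement accumulates.

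**The false-positive rates are not fixed.** Also right. A reader might infer that these tests always reject or never reject. The overall composite is planned as one model per risk, and step 7 ranges from near 0% to half or more. Infinite coefficients from complete separation arise only if baseline is coded as zero, which the protocol does not state for the composite.

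**The full analysis plan may settle the coding.** It may, but the article already fixes outcome, regressor and model, and none of the codings considered here makes that combination a test of effectiveness from baseline.

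**Conclusion.** The point holds for the change outcomes only, and should be fixed before analysis.

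Forward movement and the composite have no valid baseline value. Within baseline-stage strata, the 0% and 100% starting points follow from the definitions and need no assumption. Apparent gains in the three early strata and an apparent loss in the action stratum would arise from fluctuation alone, and without a control arm regression to the mean cannot be separated from an effect of Gabby. For the overall composite the bias is upward, about 4 to 11 points at 10% to 30% one-stage reporting error, which brackets the planned 7.3 points. That size depends on the assumed stage mix, error rate and handling of the end stages. How often a per-risk test falsely rejects depends further on the number of women per risk.

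The sample size and the leading action/maintenance comparison are not called into question here.

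**What to change.** 1. Make action/maintenance status, defined identically at all three visits, the only stage outcome regressed on time point, both as the per-woman rate and risk by risk.
2. Define forward movement and the composite explicitly relative to baseline, and report them as proportions at 3 and 5.5 months with confidence intervals clustered by end-user.
3. Replace the four stage-restricted Poisson fits with a descriptive table of baseline stage against stage at each follow-up visit.
4. State that differences between baseline-stage strata will not be interpreted as differential effectiveness. A stage-by-stage comparison with the control arm of the earlier randomised trial should not be made a condition, because the document does not show that those data are available by stage.

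The cost is a change of analysis wording and fewer formal tests. No new data are needed, since the stage reports already come from the Gabby server, and the sample size is unchanged.
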